#### Shedding criteria

2.2.4

Patients refused to cooperate with the trial after enrollment;Patients withdrew on their own during the study or did not complete the entire course of treatment and had poor compliance;Losing contact and moving to other places during treatment, and unable to cooperate with the subsequent clinical observation.

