#### Discontinuation criteria

2.2.5

Inability to tolerate needling or allergic reactions;Serious adverse events during treatment, or serious complications caused by other diseases;Female patients found to be pregnant.

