### Sample size

2.3

PASS 15.0 software was used to determine the sample size based on the nature of the study, with the control group being the healthy group and the treatment group being the insomnia group. Patients with insomnia use the PSQI score as an observed outcome indicator. Based on the pre-test results and literature review, the mean PSQI score for the drug control group is 10.76 ± 3.32 points, and it is anticipated that this score will decrease by 2.63 points for the insomnia group. The effect size (Effect Size) of the two groups is 0.8, α=0.05, Power=0.9, and this means that the sample size for the treatment group is 52 cases, and the sample size for the health group is 26 cases; taking into account variables like fewer visits, an increase in cases, and an increase in cases. The sample size for the treatment group was 52 cases, and the sample size for the healthy group was 26 instances. After taking lost visitation into account, the sample size was expanded by 15%, resulting in 66 cases for the treatment group and 33 cases for the healthy group in this experiment.

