### Blinding

2.6

By the principle of blinding, the grouping results will be blinded to the participants, acupuncturists, and evaluators. Because the acupuncture protocol was consistent in the insomnia group of this study, the acupuncturists do not need to know the grouping results and the acupuncturists cannot assess the results of the intervention. This study will be blinded to the evaluators, who will not be informed of the subgroups, will only be responsible for collecting data from the subjects, and will not be allowed to discuss the treatment with the evaluators. Because the insomnia group of this graduate student will be analyzed using a different metabolomics technique, this study will not be blinded to the metabolomics technique, and data analysts, who will be asked to perform the analysis according to their assigned group will be responsible for statistical analysis and data interpretation.

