#### Assessment time point

2.8.3

The insomnia group will have the above information completed at enrollment and after 12 treatments, the scale will be collected again at 3 months follow up, and the health group will have serum collected only at the first enrollment.

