### Quality control

2.11

PSQI, ISI, HAS, FSS, HAMA, HAMD, and MoCA scales will be evaluated by professionally qualified physicians. Standard operating procedures and quality control procedures for serum metabolomics using UPLC-Q/TOF-MS and UPLC-QQQ-MS/MS will be established, and the data will be analyzed and processed by professional instruments to ensure the accuracy of the data. The investigators signed an investigator’s declaration, received training on the trial procedure, and had their quantitative criteria for symptoms and indications validated for consistency prior to the project’s launch. In order for the subjects to cooperate with the experiment and completely grasp its requirements, the investigator must properly carry out the informed consent process. The needle counting method was used to monitor the subjects’ needle compliance. Compliance = (actual number of needles/supposed number of needles) × 100%. Compliance <80% or >120% was considered a major violation of the trial protocol.

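### Section 2.2.4 merges stopping treatment with leaving the study, so the uncontrolled PSQI change is likely to come mainly from compliant completers and may be biased, probably in favour of treatment

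*Protocol article*

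**What the plan says.** Section 2.2.4 (Shedding criteria) lists three kinds of dropout. The first is refusal to cooperate after enrolment. The second is: "Patients withdrew on their own during the study or did not complete the entire course of treatment and had poor compliance". The third is: "Losing contact and moving to other places during treatment, and unable to cooperate with the subsequent clinical observation". Only the third mentions that the patient can no longer be observed. Section 2.2.5 is a separate list for stopping on safety grounds, beginning with "Inability to tolerate needling or allergic reactions". The article does not say whether patients on either list are still assessed.

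On timing, section 2.8.3 says: "The insomnia group will have the above information completed at enrollment and after 12 treatments", with the scales repeated at three months. The abstract instead places the second assessment at four weeks, and section 2.1 places it at the end of treatment.

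On losses, section 2.3 says: "After taking lost visitation into account, the sample size was expanded by 15" per cent. Section 2.11 adds: "Compliance <80% or >120% was considered a major violation of the trial protocol". It gives no consequence for the analysis.

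On comparators, section 2.6 explains that the acupuncturist need not know the allocation: "Because the acupuncture protocol was consistent in the insomnia group of this study". Groups A and B differ only in the laboratory technique applied to their serum. The healthy group is untreated, and "the health group will have serum collected only at the first enrollment".

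**The concern.** Stopping sessions and leaving the study are different events. A patient who gives up acupuncture halfway can usually still fill in the PSQI at week 4 and month 3. The second item of 2.2.4 puts such a patient, if also poorly compliant, in the same class as someone who has withdrawn. Section 2.8.3 then defines the next assessment by a number of sessions that this patient never reaches.

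PSQI is a primary outcome, and the Discussion states efficacy assessment as an aim. No other arm could show similar attrition, so any selection among the treated patients passes straight into the mean change. If people tend to stop because they feel no benefit, the remaining patients look better than the whole group. The same patients would supply the before-after serum comparison and the correlations of metabolites with PSQI, including its follow-up values.

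This is partly a matter of trial conduct. An analysis plan can define analysis sets and missing-data methods later, but it cannot restore scales that nobody collected. The Trial Status section says recruitment is under way.

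**Working it through.** **1. The sections side by side**

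- 2.2.4, second item: shed if the course is incomplete and compliance is poor. Being unreachable is not required.
- 2.8.3: second assessment after twelve sessions. Abstract: after four weeks. At three sessions a week for four weeks the two coincide only for patients who attend on schedule. They separate for exactly the patients at issue.
- 2.3: losses are made up by enrolling more patients. Following the lost ones is not described.
- 2.11: low compliance is a major violation. Removal from the analysis is not stated.
- 2.13: only tests between two groups are named. The before-after reading of PSQI is therefore an inference from the design, in which no comparator exists for that outcome.

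Following this text literally tends to produce completer data, although no sentence requires it.

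**2. The plan's own sample size**

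Inputs from 2.3: decrease 2.63, SD 3.32, alpha 0.05, power 0.90, allocation 2:1. Two-sided testing is assumed, since the article does not state it.

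- Standardised effect: 2.63/3.32 = 0.79 (the plan rounds to 0.8).
- Healthy group: (1 + 1/2) × (1.960 + 1.282)² / 0.792² = 25.1, rounded up to 26. Treated: 2 × 26 = 52.

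The stated 52 and 26 reproduce. With the t distribution, power at 52 and 26 is 0.903.

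**3. Which loss fraction to use**

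The stated allowance is 15%. It does not itself lead to 66 and 33: 26/0.85 = 30.6, rounded up to 31, gives 62 and 31; 26 × 1.15 = 29.9, rounded up to 30, gives 60 and 30. The margin from 66 to 52 is 14/66 = 21.2%, but the article never states this as a loss rate. The mismatch is a separate arithmetic matter, so 15% is used below. Of 66 patients, 15% is about 10, leaving about 56.

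**4. Possible size of the bias (illustration)**

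Assume completers improve by 2.63 points, a fraction f = 0.15 is shed and left out, and shed patients would have improved by c. The article gives no value for c.

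All-patient improvement = (1 − f) × 2.63 + f × c

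Overstatement = f × (2.63 − c)

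| c (points) | All-patient improvement | Overstatement | Relative to all patients |
|---|---|---|---|
| 2.63 (same as completers) | 2.63 | 0 | 0% |
| 1.315 (half) | 0.85 × 2.63 + 0.15 × 1.315 = 2.43 | 0.20 | 8% |
| 0 (no change) | 0.85 × 2.63 = 2.24 | 0.39 | 18% |

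If shed patients improve by more than 2.63, the sign reverses.

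**5. How much follow-up could recover**

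Not every shed patient can be followed. Suppose half of the 15% are assessed and show no change, while the other half remain missing. The observed mean is then (0.85 × 2.63)/(0.85 + 0.075) = 2.2355/0.925 = 2.42, and the correction is 2.63 − 2.42 = 0.21 points rather than 0.39.

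**The case against.** The strongest reply is that the harm is inferred. Section 2.2.4 says who counts as a dropout. It does not say that their scales go uncollected or that they leave the analysis. Analysis sets and missing-data methods are commonly left to a full protocol or analysis plan, and neither is shown. A reader might infer that the PSQI result is defined on completers and must overstate the benefit. The documents do not support that, for four reasons:

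- The second item joins incomplete treatment to poor compliance, so not finishing the course may not be enough on its own to make a patient a dropout.
- The abstract and section 2.1 give timings that do not depend on attendance, and the reference to twelve treatments in 2.8.3 can be read as naming the end of the planned course.
- The 15% allowance does not refer to 2.2.4, and a recorded protocol violation is compatible with keeping the patient in the analysis.
- No section gives reasons for stopping. Patients who stop because they feel well would push the bias the other way.

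It is also fair to say that the missing comparator limits any PSQI efficacy claim more than this rule does, and that rewording 2.2.4 would not cure it.

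All of this stands, and it makes the bias conditional. It does not remove the point. The rule on the page merges two events that should be kept apart, the assessment trigger in 2.8.3 conflicts with the abstract for the affected patients, and data not collected cannot be supplied by a later document.

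**Conclusion.** The point holds as a risk created by the stated rule and the assessment trigger. It is not a demonstrated exclusion. Read as written, the post-treatment PSQI and serum data are likely to come mainly from compliant completers, and the uncontrolled PSQI change may then be biased, probably in favour of treatment.

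Under the 15% allowance and a completer improvement of 2.63 points, the overstatement lies between 0 and 0.39 points if shed patients' true change lies between full improvement and none. The upper figure is 0.39/3.32 = 0.12 of the planning SD, so it would distort the estimate modestly rather than create an effect from nothing. Follow-up could correct only part of it if some patients remain out of reach. The direction rests on the assumption that those who stop do less well, which the documents neither state nor contradict. A larger figure based on a 21% loss would rest on a loss rate that the article does not state.

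Confidence is medium. An amendment is worthwhile because it is cheap and the data concerned cannot be recovered later.

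**What to change.** Split section 2.2.4 in two:

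- **(a) Treatment not completed or poor compliance.** The patient remains in the study, completes the scales at calendar week 4 and month 3 (remotely where the scale allows), gives the week-4 serum if willing, and is included in the primary PSQI analysis.
- **(b) Consent withdrawn or contact lost.** Data up to that point are used.

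In 2.8.3, anchor the second assessment to calendar week 4 rather than to twelve completed sessions, so that it agrees with the abstract. In 2.11, state that the 80% compliance limit serves only to define a sensitivity set. These changes concern data collection and analysis. They leave decisions about continuing or stopping treatment as they are.

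The cost is one amended paragraph, one aligned sentence on timing and some extra follow-up contacts. The mean change may come out smaller, but it would describe the enrolled patients better. If the sponsor already follows such patients, the amendment only makes the text say so.

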#### Discontinuation criteria

2.2.5

Inability to tolerate needling or allergic reactions;Serious adverse events during treatment, or serious complications caused by other diseases;Female patients found to be pregnant.

### Sample size

2.3

PASS 15.0 software was used to determine the sample size based on the nature of the study, with the control group being the healthy group and the treatment group being the insomnia group. Patients with insomnia use the PSQI score as an observed outcome indicator. Based on the pre-test results and literature review, the mean PSQI score for the drug control group is 10.76 ± 3.32 points, and it is anticipated that this score will decrease by 2.63 points for the insomnia group. The effect size (Effect Size) of the two groups is 0.8, α=0.05, Power=0.9, and this means that the sample size for the treatment group is 52 cases, and the sample size for the health group is 26 cases; taking into account variables like fewer visits, an increase in cases, and an increase in cases. The sample size for the treatment group was 52 cases, and the sample size for the healthy group was 26 instances. After taking lost visitation into account, the sample size was expanded by 15%, resulting in 66 cases for the treatment group and 33 cases for the healthy group in this experiment.

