### Study design

2.1

The study design is a single-center, double-blind, clinical trial to investigate the metabolic pathways and possible mechanisms underlying the efficacy response of electroacupuncture for insomnia. The study protocol follows the SPIRIT guidelines, 99 subjects will be recruited and divided into an insomnia group and a healthy group. The International Classification of Sleep Disorders, Third Edition (ICSD-3) diagnostic criteria will be used to diagnose subjects with insomnia. Those who meet the inclusion criteria will also sign an informed consent form, complete the following scale assessments, and have their serum collected: PSQI and ISI to measure sleep; HAS to measure hyperarousal state; HAMD and HAMA to measure mental state; and FSS to measure physical and mental fatigue, sleep diary to measure sleep behavior, and MoCA to measure cognition to gather baseline assessment data. This will be followed by 4 weeks of treatment. Retesting of the above scales will be completed at the end of treatment and at 3 months follow-up, as well as serum collection’s will be completed at the end of treatment. The healthy group will complete serum collection at enrollment. The insomnia group will be randomly divided into Group A and Group B, matched with the healthy group. Group A and the healthy group will be screened for differential metabolites using metabolomics analysis with non-targeted UPLC-Q/TOF-MS, and Group B will be quantified for the screened differential metabolites using metabolomics with targeted UPLC-QQQ-MS/MS. The flow chart of the experiment is shown in **Figure 1**. The flow schedule is shown in **Figure 2**.

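### The 90% power in section 2.3 belongs to a two-sample PSQI comparison that the trial cannot make, and the stated 15% expansion does not turn 52/26 into 66/33

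*Protocol article*

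**What the plan says.** Section 2.3 (Sample size) sets up a two-group calculation, "with the control group being the healthy group and the treatment group being the insomnia group", with PSQI as the outcome. The mean and SD come from elsewhere: "the mean PSQI score for the drug control group is 10.76 ± 3.32 points". The effect is given as "it is anticipated that this score will decrease by 2.63 points for the insomnia group", and the design values as "The effect size (Effect Size) of the two groups is 0.8, α=0.05, Power=0.9". The result is "the sample size for the treatment group is 52 cases, and the sample size for the health group is 26 cases". Losses are then allowed for: "the sample size was expanded by 15%, resulting in 66 cases for the treatment group and 33 cases for the healthy group".

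Other sections describe what is measured and compared:

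- Section 2.8.3 (Assessment time point) and the abstract schedule the scales for the insomnia group. For the controls, "the health group will have serum collected only at the first enrollment".
- Section 2.1 (Study design) gives the case-control comparison: "Group A and the healthy group will be screened for differential metabolites using metabolomics analysis with non-targeted UPLC-Q/TOF-MS".
- Section 2.6 (Blinding) says that acupuncture is the same throughout the insomnia group, and section 2.7.2 that the healthy group is untreated.
- Section 2.8.1 names two primary outcomes, PSQI and metabolomics.
- Section 2.5 (Randomization) has 33 insomnia patients divided 1:1 into A and B, whereas the abstract and section 2.3 have 66.

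**The concern.** A sample-size statement should refer to a comparison that the trial will carry out. Here the nominal comparator is the healthy group, the numerical comparator is a drug-treated group, and neither supplies PSQI data for a test against the insomnia group. A reader who sees 90% power beside two primary outcomes will assume that it covers at least one of them.

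The loss allowance has a separate fault: the percentage given is not the one that produces the recruitment target. Anyone judging whether attrition stayed within plan would use the wrong yardstick.

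**Working it through.** **Inputs from section 2.3.** Difference 2.63; SD 3.32; stated effect size 0.8; alpha 0.05 (sidedness not given there); power 0.90; 52 and 26 before losses; 15%; 66 and 33 after.

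**1. Reproducing 52/26.** Effect d = 2.63/3.32 = 0.792. With treated:control ratio k = 2 and a two-sided test, the normal approximation is n(control) = (1.960 + 1.282)² × (1 + 1/k)/d².

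- d = 0.792: 10.51 × 1.5/0.6275 = 25.1, so 26 and 52.
- d = 0.8: 10.51 × 1.5/0.64 = 24.6, so 25 and 50.
- Exact noncentral t: 25.8/51.5 at d = 0.792 and 25.3/50.6 at d = 0.8. Both round up to 26/52.
- Exact power at 52 vs 26: 0.903 (d = 0.792) and 0.908 (d = 0.8).
- A one-sided test gives 21/42, which does not fit.

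So the calculation is a two-sided, 2:1, two-sample test of PSQI means.

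**2. Looking for that comparison in the trial.**

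| Possible PSQI contrast | Available? |
|---|---|
| Insomnia vs drug control | No drug arm |
| Insomnia vs healthy | No PSQI planned for the healthy group in the text |
| Group A vs Group B | Both receive the same treatment, so no treatment effect to detect |
| Within patients, before vs after | Yes, but a paired comparison, not the one calculated |

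**3. The expansion.**

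- Multiplying by 1.15: 52 × 1.15 = 59.8 and 26 × 1.15 = 29.9, so 60/30 (total 90).
- Dividing by 0.85: 52/0.85 = 61.2 and 26/0.85 = 30.6, so 62/31 (total 93).
- Implied by 66/33: 66/52 = 1.269, a 27% expansion; 1 − 52/66 = 0.212, a 21% loss allowance.

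**4. Paired PSQI change.** The SD of change is not given. Assume SD 3.32 at both visits and correlation r, so SD of change = 3.32 × √(2(1 − r)). Take 2.63 as a within-patient change. Exact two-sided power at 0.05:

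| r | SD of change | n = 52 | n = 66 |
|---|---|---|---|
| 0 | 4.70 | 0.977 | 0.994 |
| 0.3 | 3.93 | 0.997 | >0.999 |
| 0.5 | 3.32 | >0.999 | >0.999 |
| 0.7 | 2.57 | >0.999 | >0.999 |

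**5. Group A vs healthy, per metabolite.** No metabolite effect or SD is given, so the detectable effect is the meaningful quantity. The last column borrows the PSQI value of 0.8 for illustration only. Exact t, two-sided 0.05, unadjusted:

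| Sizes | Effect detectable with 90% power | Power at borrowed 0.8 |
|---|---|---|
| 33 vs 33 (as planned) | 0.81 SD | 0.893 |
| 28 vs 28 (15% lost in both) | 0.88 SD | 0.836 |
| 26 vs 26 (21% lost in both) | 0.92 SD | 0.807 |

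If section 2.5 is taken literally, Group A has 16 or 17 patients, and power at the borrowed 0.8 against 33 healthy is 0.73 to 0.75.

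**The case against.** The strongest reply is that no power is lost. The expansion error enlarges the sample, the paired PSQI analysis is well powered under reasonable assumptions, and section 2.3 names PSQI as its outcome and claims nothing for metabolomics. All of that stands. It limits the consequence but does not give the 90% an analysis to belong to.

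A reader might infer that the comparison actually made has about 81% power instead of 90%. The documents do not support that. The 81% needs both groups to fall to 26. The healthy group gives one sample at enrolment and has no follow-up to lose, and patients' serum is also taken at baseline, so 33 vs 33 and about 89% is the natural case, within a point of 90%. Every such figure also transfers a PSQI effect size to metabolites, for which the protocol gives none. Nor can a multiplicity-adjusted figure be derived: the introduction's 328 metabolites is a literature count, not the number of tests here.

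It could also be said that the schedule figure, not visible here, might show a baseline PSQI for the healthy group. Even so, a patient-versus-healthy difference would not be the 2.63-point effect that was calculated.

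**Conclusion.** The point holds in two parts, and both rest on the protocol's own figures. First, the 90% power describes a two-sample PSQI contrast that the trial does not make, which leaves the metabolomic primary outcome without a sample-size basis. Second, 15% yields 60 to 62 and 30 to 31, so 66/33 overshoots the stated rule by 4 to 6 patients and 2 to 3 controls.

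This does not show that 99 participants are too few. Paired PSQI power of about 0.98 or more assumes that 2.63 is a within-patient change, that the SD is 3.32 at both visits and that the correlation lies between 0 and 0.7. Section 2.3 leaves open whether 2.63 is a change or a between-group difference. The metabolomic figures assume 33 patients in Group A, which section 2.5 puts in doubt, and they worsen with any multiplicity control.

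**What to change.** Keep N = 99 and rewrite section 2.3:

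- **PSQI.** Withdraw the two-sample 90% claim. Base power on the within-patient change from baseline to week 4. State the assumed SD of change, and say whether 2.63 is a within-patient change or a between-group difference, with its source.
- **Metabolomics.** For Group A vs healthy on baseline serum, state a detectable effect instead of a power: 0.81 SD per metabolite at 33 vs 33, unadjusted, with 90% power. Add that it is larger after losses or multiplicity control.
- **Losses.** State the allowance as 21% (a 27% expansion), which is the one used, and apply that single rate throughout.
- **Group A.** Reconcile the 33 patients in section 2.5 with the 66 in the abstract and section 2.3, since this sets the size of Group A.

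The cost is a text amendment and a less tidy power statement. It needs no extra participants.
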